## Abstract

**Introduction:**

Levels of stress in UK university students are high, with an increase in the proportion of students seeking help in recent years. Academic pressure is reported as a major trigger. Mindfulness training has been shown to reduce stress and is popular among students, but its effectiveness in this context needs to be ascertained. In this pragmatic randomised controlled trial, we hypothesise that the provision of a preventative mindfulness intervention in universities could reduce students' psychological distress during the examination period (primary outcome), improve their resilience to stress up to at least 1 year later, reduce their use of mental health support services and improve academic performance.

**Methods and analysis:**

At least 550 University of Cambridge students free from active crises or severe mental illness will be randomised to joining an 8-week mindfulness course or to mental health provision as usual (one-to-one allocation rate). Psychological distress will be measured using the Clinical Outcomes in Routine Evaluation Outcome Measure at baseline, postintervention, examination term and 1-year follow-up. Other outcomes are use of mental health services, inability to sit examinations or special circumstance requests, examination grades, well-being, altruism and coping measured with ecological momentary assessment. Outcome assessment and intention-to-treat primary analysis using linear mixed models adjusted for baseline scores will be blind to intervention allocation. We will also conduct per-protocol, subgroup and secondary outcome analyses. An Independent Data Monitoring and Ethics Committee will be set up. We will systematically monitor for, and react to, possible adverse events. An advisory reference group will comprise student representatives, members of the University Counselling Service and other student welfare staff.

**Ethics and dissemination:**

Approval has been obtained from Cambridge Psychology Research Ethics Committee (PRE.2015.060). Results will be published in peer-reviewed journals. A lay summary will be disseminated to a wider audience including other universities.

**Trial registration number:**

ACTRN12615001160527; pre-results.

Strengths and limitations of this studyOne of the largest randomised controlled trials assessing mindfulness interventions and the largest involving students, to date.A pragmatic design evaluating the provision of a service, intended to inform university student welfare policies in the global context of massively increasing participation in higher education.Interdisciplinary team and horizontal co-production of research question and study design between researchers and stakeholders.Study design assesses the effectiveness of mindfulness (ie, whether it produces the expected results under ‘real-world’ settings), but does not test its efficacy (ie, whether mindfulness produces the expected results under ideal circumstances, such as perfect course attendance), or determine its specific effects.

## Introduction

### Background and rationale

University students show elevated levels of stress. Although mental illness rates among first year students appear to be lower than those of the general population, they surpass general population rates when undergraduates get to their second year.^1^ Students report academic pressure as the biggest trigger of their mental health problems.^2^ University Counselling Services in the UK have noted the constant increase in the proportion of students seeking help in recent years.^3^
^4^ At the University of Cambridge, 8.5% of the students required access to counselling in 2014. An effective preventative intervention is needed to help students cope better with academic life and develop resilience.

Mindfulness interventions have been shown to reduce stress and prevent depression in clinical and non-clinical populations.^5^
^6^ Secular mindfulness training involves paying attention to the present moment on purpose and non-judgmentally.^7^ It is popular among students and increasingly used to support them in the UK.^8^ However, there is little evidence on the effectiveness of offering mindfulness training to this population or of any adverse effects. Previous randomised trials assessing mindfulness for supporting university students generally suffer from small sample sizes, lack of follow-up, low methodological quality and poor reporting.^9^ The largest good-quality study randomised 288 medical and psychology Norwegian students to mindfulness-based stress reduction or a waitlist and found moderate postintervention effects on psychological distress and subjective well-being.^10^ A recent systematic review which meta-analysed nine randomised and non-randomised studies found that mindfulness significantly reduced anxiety among university students (d=0.73; 95% CI 1.00 to 0.45).^11^ A good-quality and adequately powered randomised evaluation including the wider spectrum of university students is needed to confirm previous findings, extend the follow-up period and provide a more complete view of the potential impact (positive and negative) of the provision of mindfulness training on university student life. The University of Cambridge Vice-Chancellor's Endowment Fund is supporting such evaluation for use by services, funders and policymakers, as well as to inform the University's own decisions about the provision of mindfulness for students.

### Objectives

The proposed study aims to evaluate whether the provision of a mindfulness course to higher education students:
Helps them to manage stress during the examination period;Improves their mental well-being and resilience to stress up to 1 year later;Reduces their use of mental health treatment and support services;Improves their engagement with student life, including their academic performance.

Our main hypothesis is that the provision of mindfulness training will reduce students' psychological distress during the examination period in comparison with students who have not been offered this provision.

### Trial design

The study will be a pragmatic randomised controlled evaluation with two parallel arms and a one-to-one allocation rate testing the superiority of mindfulness training provision to no provision. University of Cambridge students will be randomised to joining a mindfulness course during the term they are starting plus mental health provision as usual (PAU), or to PAU alone. PAU comprises access to individual counsellors, mental health advisors and psychiatrists at the University of Cambridge Counselling Service (UCS), as well as access to welfare staff in the University colleges (this provision varies across colleges, but can include college nurse, counsellor, welfare officer or tutor) and National Health Services (NHS). Those allocated to PAU alone will be offered a mindfulness course 1 year later, providing they are still students at the University.

The mindfulness intervention was offered for two terms before study initiation; this allowed the intervention to become established before evaluating it, and provided feasibility and acceptability data. The present proposal is partly based on the experience during those two terms. Interest in the courses doubled teaching capacity. An opportunistic randomised evaluation was therefore considered reasonable.

## Methods

This protocol was prepared in accordance with SPIRIT 2013 statement.^12^ The SPIRIT checklist is available as an online supplementary file. The trial registration process (ACTRN12615001160527) needs clarification. The protocol was submitted to the trial registry in time for prospective registration but an unforeseen delay at their fault led to a final retrospective registration date. This problem was acknowledged by the trial registry and did not increase risk of bias compared with routine prospective registration.

10.1136/bmjopen-2016-012300.supp1supplementary file

### Eligibility criteria

Participant eligibility criteria for this study are unchanged from those used routinely by the UCS for mindfulness courses. They are all self-reported. The inclusion criteria are as follows:
Undergraduate and postgraduate University of Cambridge students in any year or course;Who consider they can realistically attend at least seven sessions of the course.

The exclusion criteria are as follows:
Currently suffering from severe periods of anxiety or depression;Experiencing severe mental illness such as hypomania or psychotic episodes;Following recent bereavement or major loss;Experiencing any other serious mental or physical health issue that would impact on their ability to engage with the course.

Students will be advised to contact the study team if they are unsure about their eligibility.

### Intervention

The 8-week mindfulness course is called ‘Mindfulness Skills for Students’. It consists of a secular, group-based skills training programme based on the course book ‘Mindfulness: A Practical Guide to Finding Peace in a Frantic World’,^13^ and adapted for university students. This intervention aims to optimise experiences across a range of students and is not specifically developed for those students in the clinical range.

The sessions last for 90 min for the first session, and 75 min for the remaining sessions. There are eight weekly sessions, all run by [name], an experienced and certified mindfulness teacher. Each session includes two mindfulness meditations, the first embedding the meditation that the students have practised at home throughout the week; the second, introducing them to the new meditation that they will practice at home in the coming week. There are also periods of reflection and inquiry, helping the students to understand the nature of mindfulness, to deepen their learning and embed it into their everyday lives. A few simple models are used and developed throughout the course, to give the students some theoretical understanding of the concepts developed experientially. As is usual in mindfulness programmes, each session also includes interactive exercises, so that the students share their experience and get to know each other throughout the course, building a sense of safety and community.

Before and after each class, students receive an email from the mindfulness teacher. This reminds them of the themes covered in the previous class, and lets them know the topics coming up in the next class. These emails also include handy tips, poems and video clips. There is also a course handout available in hardcopy at each class that can also be downloaded via a link in the postclass email, which describes the home practice for the coming week. The home practice time varies through the course, starting at 8 min, and increasing to about 15–25 min/week plus ongoing reflection through the day. It includes meditations from the course book's compact disc and other mindfulness practices such as a mindful walk, mindful eating, habit breakers and so on. More practice is possible for those who want it, and students are encouraged not to miss a day, but to rather consider doing less on days when they are busy. A detailed intervention manual is available on request from the corresponding author.

Seven Mindfulness Skills for Students courses run in parallel each term (which only lasts 9 weeks in Cambridge) with up to 30 students each. Students need to choose a session time and day to attend each week but are encouraged to attend as many sessions as they can, so if they cannot make their usual session, they can attend an alternative session within the same week (session hopping). Students are contacted by email when they miss a session to check whether the absence is related to a negative experience with mindfulness and, subsequently, to offer support.

As this will be a pragmatic study, care will be taken not to interfere with or modify routine practices for intervention delivery. Therefore, there will be no ad hoc adherence optimisation procedures. Participants in the control group will be guaranteed a space in the following year's mindfulness course and will be requested to inform the research team should they decide to learn mindfulness elsewhere during the follow-up period.

### Outcomes and data collection

Several outcomes will be measured and compared between mindfulness and control groups to assess the effects of the course. The primary outcome will be a self-reported global measure of psychological distress assessed during the examination term, the most stressful period of Cambridge students' academic year. Secondary outcomes are exploratory assessments that may help to describe mindfulness' effects in more focused ways. Outcomes are listed in table 1.

**Table 1 BMJOPEN2016012300TB1:** MSS study outcomes

Outcome	Source/measure	Variable type	Collection points
Use of mental health services	Self-reported	Nominal	One-year follow-up
Use of University Counselling Service	Routinely collected	Nominal	Baseline, 1-year follow-up
Perceived impact of problems on academic performance	Self-reported	Ordinal	Examination term
Examination grades and rankings	Routinely collected	Ordinal	Examination term
Special circumstances requests for examinations	Routinely collected	Nominal	Examination term
Inability to sit examinations (intermissions and degrading)	Routinely collected	Nominal	Examination term
Psychological distress	Self-reported: CORE-OM	Treated as interval	Baseline, postintervention, examination term, 1-year follow-up
Well-being	Self-reported: WEMWBS	Treated as interval	Baseline, postintervention, examination term, 1-year follow-up
Altruism	Behavioural	Ordinal	Postintervention, examination term, 1-year follow-up
Coping	Self-reported	Ordinal	Baseline (Lent), examination term
Physical activity	Behavioural (sensor)	Ratio	Baseline (Lent), examination term
Sleep times	Behavioural (sensor)	Ratio	Baseline (Lent), examination term

CORE-OM, Clinical Outcomes in Routine Evaluation Outcome Measure; MSS, Mindful Student Study; WEMWBS, Warwick-Edinburgh Mental Well-being Scale.

Psychological distress will be measured using the Clinical Outcomes in Routine Evaluation Outcome Measure (CORE-OM), a 34-item generic questionnaire which was designed to assess efficacy and effectiveness across multiple disciplines offering psychological therapies, and has been widely used with UK university students. It is scored on a five-point scale ranging from 0 (not at all) to 4 (most or all the time). The total score range is 0–136; this is usually divided by number of completed items to form a total mean score. CORE-OM has good convergent validity, internal and test–retest reliability and sensitivity to change.^14^

Students' subjective well-being will be assessed using the Warwick-Edinburgh Mental Wellbeing Scale (WEMWBS), a questionnaire that captures a broad conception of well-being. It consists of 14 items, each scored on a five-point scale ranging from 1 (none of the time) to 5 (all of the time). The WEMWBS has good validity, internal consistency and test–retest reliability with a sample of UK students (n=354) and general population (n=2075).^15^

Mental health services use will be assessed by asking students whether during the examination term they have requested help with mental health issues and stress from a range of resources (eg, psychiatrist, Samaritans). Participants will also be asked to what extent such problems may have impacted on their academic performance (eg, To what extent do you have problems affecting your study?) and whether in their view their academic course workload was manageable. Data on inability to sit examinations will be provided by the Student Registry. The UCS will provide the research team with information about which participants used their services and how frequently they were used.

Day-to-day coping during the examination period will be assessed by applying ecological momentary assessment based on the cognitive appraisal theory of coping.^16^ Every morning for 2 weeks, six questions will be asked about coping with academic stress on the previous day. These data will also be collected for a week at baseline from the participants recruited in January 2016. Motivational relevance (How motivated did you feel by academic matters yesterday?, How stressed did you feel by academic matters yesterday?), problem-focused coping potential (Did you study as much as you had planned yesterday?, Did you take as many breaks from study as you had planned yesterday?) and emotion-focused coping potential (How satisfied with yourself are you about the amount you studied yesterday?, How satisfied with yourself are you about the breaks from study you took yesterday?) will be assessed. Participants with an Android smartphone will be able to install a free application (‘EasyM’, developed by the University of Cambridge Computer Laboratory^17^) that will send notifications and display the questions. Other participants will receive a text message notification with a link to an online survey. In order to see how disrupted students' healthy routines become during the examination period, physical activity and sleep pattern data will be passively collected from Android users by the EasyM app using movement sensors (built-in accelerometer) for 2 weeks.

In view of evidence that mindfulness may stimulate altruism,^18^ and that altruistic actions are associated with increased well-being,^19^ we are exploring altruistic behaviour differences between groups. A sum of money in the form of Amazon vouchers will be offered to participants after completing each questionnaire (£3 for postintervention and 1-year follow-up questionnaires, £5 for the examination term questionnaire which will measure the primary outcome). A choice will be given as to whether to keep the token or to donate it to a local mental health charity. This will constitute an objective measure of altruism.

Process measures will involve: (1) registering attendance at mindfulness courses (register taken) and asking why sessions were missed (routine practice for UCS); (2) asking students whether they did their mindfulness homework during the course and how much they have practised after the course, including whether they became members of the Mindfulness Society; (3) for students who abandon the study (ie, fail to complete questionnaires or contact us saying they wish to quit the study), information on why they have done so will be requested; (4) participants in the control group will be asked whether they have practised mindfulness elsewhere during the follow-up period.

Apart from the baseline measurements outlined in table 1, the following baseline data will be collected in order to compare the sample with the student population, and to run subgroup analyses: (1) students' prior experience with meditation and mindfulness; (2) demographic data provided by the student registry (eg, disability, ethnicity, socioeconomic classification). All baseline data will be collected before randomisation.

Questionnaires will be web-based. Privacy issues related to accessing student records and collecting data from smartphone sensors were explored in a focus group with students who completed mindfulness courses taught before the trial. Students felt these methods were acceptable.

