### Blinding and randomisation procedures

After agreeing to take part, students will be emailed with a link to the online baseline questionnaire. Only those who complete the baseline questionnaire will be randomised. Simple randomisation will be carried out remotely by the survey software (Qualtrics) using computer-generated random numbers. Participants will be informed of their allocation automatically after completing the baseline questionnaire. This way the allocation process will be concealed from researchers.

Participants randomised to the intervention group will be requested to state which of the seven mindfulness session times on offer they would be able to attend. Then, to minimise attrition, an allocation optimisation programme will be run with these data to assign as many students as possible to one of their preferred course times.

Participants cannot be blind to allocation because of the nature of the intervention. However, outcome assessment will be blind because data collection is carried out remotely and automatically. The primary analysis will be carried out by a statistician blind to which arm is the intervention, and other variables/information which could be used to identify intervention arm data. Mindfulness courses will include participants who are not part of the trial (consisting of up to 60 interested students distributed evenly across courses so that 4–5 students out of 30 per course are not part of the study), and the mindfulness teacher will not be told who is and who is not a participant in the study.

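### A cheap, minor gain is missed: self-reported service use and perceived impact on study are not measured before randomisation, although every participant completes a web baseline

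*Protocol article*

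**What the plan says.** All references are to the Methods of the protocol article.

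- **Outcomes and data collection, Table 1.** "Use of mental health services" (self-reported, nominal) has a single collection point, "One-year follow-up". "Perceived impact of problems on academic performance" (self-reported, ordinal) also has one, the examination term. CORE-OM, WEMWBS and routinely collected counselling-service use all have a baseline.
- **Same section, text on baseline data.** The sentence beginning "Apart from the baseline measurements outlined in table 1, the following baseline data will be collected" goes on to name prior meditation experience and registry demographics. Neither of the two outcomes is among them.
- **Same section, on timing and mode.** "All baseline data will be collected before randomisation", and "Questionnaires will be web-based".
- **Blinding and randomisation procedures.** "Only those who complete the baseline questionnaire will be randomised". Randomisation is simple, with no stratification stated.
- **Objectives.** The third aim is whether the course "Reduces their use of mental health treatment and support services".
- **Same outcomes section, text on service use.** The self-report question covers help sought from a range of sources during the examination term, whereas Table 1 places its collection at 1 year.

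**The concern.** A student's earlier help-seeking, and earlier problems affecting study, plausibly predict the later answers to the same questions. The plan uses this principle for its primary outcome, where the CORE-OM comparison is adjusted for the baseline score. For these two self-reports it cannot do so, because the collection schedule provides no baseline value. No later analysis plan can adjust for an answer that was never collected.

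At stake is precision on outcomes that serve the third objective and part of the fourth. There is also a descriptive gap. Counselling-service records show prior use of one source, while the self-report asks about several. The article will therefore be unable to say how many participants in each arm were already receiving help elsewhere at entry.

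**Working it through.** **The plan's own figure.** The article gives no power or precision figure for these two outcomes. Its only calculation is for CORE-OM: 550 randomised, 0.3 SD, 90% power, two-sided 5%, 20% loss. After loss, 550 × 0.8 = 440 are evaluable, or 220 per arm. Power at 0.3 SD is then Φ(0.3/√(2/220) − 1.96) = 88.2%, close to the stated 90%. Only the 220 per arm is used below.

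**Is the comparison valid without a baseline?** Yes. A simulation of 20,000 null trials with 440 evaluable students and a baseline-outcome correlation of 0.5 gave an unadjusted bias of about 0 and a type I error of 5.3%.

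**Precision, against no covariate.** Adjusting for a baseline with correlation r multiplies the variance by 1 − r². The article gives no r, so a range is assumed, on a continuous-scale approximation:

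| r | Variance removed | SE reduction | 440 act like 440/(1 − r²) | Power at 0.2 SD (55.5% unadjusted) |
|---|---|---|---|---|
| 0.3 | 9% | 5% | 484 | 59.4% |
| 0.5 | 25% | 13% | 587 | 67.8% |
| 0.6 | 36% | 20% | 688 | 74.6% |

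**Precision, when a related baseline is already adjusted for.** Let a be the correlation of the outcome with its own baseline, b its correlation with the related baseline, and c the correlation between the two baselines. Then R² = (a² + b² − 2abc)/(1 − c²), and the SE is multiplied by √[(1 − R²)/(1 − b²)]. All values are assumed.

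- a = 0.3, b = 0.3, c = 0.5: R² = 0.120, factor √(0.880/0.910) = 0.983, a further reduction of 2%.
- a = 0.6, b = 0.4, c = 0.5: R² = 0.373, factor √(0.627/0.840) = 0.864, a further reduction of 14%.

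**Service use as a binary outcome.** Assume 20% prior users, control-arm later use of 50% in prior users and 12.5% in others, and a 40% relative reduction in both groups.

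- Control: 0.2 × 0.5 + 0.8 × 0.125 = 0.20. Intervention: 0.6 × 0.20 = 0.12. Difference: 8 points.
- Unadjusted SE = √[(0.20 × 0.80 + 0.12 × 0.88)/220] = √(0.2656/220) = 0.0347. Power = Φ(0.08/0.0347 − 1.96) = 63%.
- Prior use has variance 0.2 × 0.8 = 0.16. Its slope is 0.375 in controls and 0.225 in the intervention arm, 0.30 on average. Residual variances are 0.16 − 0.16 × 0.375² + 0.16 × 0.075² = 0.1384 and 0.1056 − 0.16 × 0.225² + 0.16 × 0.075² = 0.0984, which sum to 0.2368.
- Adjusted SE = √(0.2368/220) = 0.0328. Power = Φ(0.08/0.0328 − 1.96) = 68%.

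With 8.5% prior users (the 2014 counselling rate in Background and rationale, which covers one source only) and the other assumptions unchanged, the same steps give about 51% rising to 54%, a gain of about 3 points.

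**Chance imbalance is the same cost, not a second one.** The SD of the between-arm difference in prior users is √(2 × 0.16/220) = 0.0381. Multiplied by the average slope of 0.30, this is 0.0114, or 1.1 points. Then √(0.0328² + 0.0114²) = 0.0347, which is the unadjusted SE. The unadjusted confidence interval therefore already allows for this imbalance.

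**The case against.** A randomised comparison does not need a baseline for each secondary outcome, and the article contradicts nothing by leaving these out. Both outcomes belong to a set that it describes as exploratory. Each objective also rests on other measures: counselling-service use, which has a baseline, and grades, special-circumstances requests and inability to sit examinations. Baseline CORE-OM, WEMWBS and counselling-service use are available to any analysis, and nothing in the article rules them out as covariates here. All of this stands. It makes the point minor, and it is why the 2% to 14% range is given.

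The proposed baseline items would also cover a different period from the outcome. A first-year student recruited in October has no Cambridge workload to report, and this lowers the correlation for part of the sample. That stands too, and it limits the fix. It does not remove the point: help-seeking over a stated past window, and whether problems are currently affecting study, can be asked of anyone before allocation.

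A reader might infer that, with simple randomisation, the missing baselines leave the two comparisons biased or open to an imbalance that cannot be handled. The documents do not support that. The estimates are unbiased, the confidence intervals include chance imbalance, and related baselines can recover part of the loss.

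**Conclusion.** The omission is real and fixed by Table 1, and its consequence is minor. Two exploratory self-reported outcomes will be compared less precisely than they could be, and prior help-seeking outside the counselling service will go undescribed. The gain forgone is 9% to 36% of the variance against no covariate, or a further 2% to 14% of the SE beyond a related baseline. In the service-use scenarios it is about 3 to 5 points of power. These sizes rest on assumed correlations, prevalences and effects, since the article gives none. With r of 0.3 or less the gain is small.

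It would go too far to conclude that the third objective cannot be assessed because new help-seeking is not separated from continuing care. That objective asks about reduced use, which the randomised comparison addresses directly. A baseline would help to describe and interpret the result.

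**What to change.** 1. First reconcile the examination-term recall period given in the text on service use with the 1-year collection point in Table 1, so that the outcome window is defined.
2. Add the service-use checklist, over a stated past window, and the present-tense item on problems affecting study to the pre-randomisation web form. Leave out the workload item for students with no prior course workload.
3. Add a baseline collection point to both Table 1 rows.
4. Use each baseline answer as a covariate in the between-arm analysis of its own outcome.

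The cost is one or two minutes of participant time at enrolment and one extra covariate per model. The gain will be smaller for students who are new in October. The items need to be in place before allocation: asked later, they would be answered by participants who already know their arm.
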